### Primary outcome

The primary outcome is the:

#### Modified Action Research Arm Test (ARAT) for the target hand at 8 weeks

The ARAT is a standardised measure of unilateral hand and upper limb function. It consists of four sub-tests including grasp, grip, pinch and gross movement. Participants will be required to perform every task in each subtest [12]. All tasks will be scored on a 4-point scale from 0 to 3 where 0 reflects poor hand function and 3 reflects good hand function. Scores will be summed to give a total possible score of 57 where a larger number reflects better hand function. The modified non-standardised table height will be used and testing will be done in a seated position. Although the ARAT was originally used as a measure of arm and hand function after stroke,[13] it has been successfully used in a trial similar to this one conducted in people with established SCI [personal communication; [name], 2009]. The ARAT has excellent reliability and has been validated against a number of other upper limb function tests [14-17]. It also has good face validity, assessing a range of functional hand tasks.

### Secondary outcomes

The secondary outcomes are the:

#### Modified Action Research Arm Test (ARAT) for the target hand at 6 months and 12 months

The ARAT will be performed and scored as described above.

#### Summed Upper Limb Strength of the target hand at 8 weeks, 6 months and 12 months

The strength component of the Graded and Redefined Assessment of Strength, Sensibility and Prehension (GRASSP) will be used to assess upper limb strength of the target hand [18]. This consists of a 6-point manual muscle test [19] to score the following nine joint actions: shoulder flexion, elbow flexion, elbow extension, wrist extension, finger flexion, finger extension, finger abduction, thumb flexion, and thumb opposition. Scores will be summed to give a total possible score of 65 where a higher score indicates better strength than a lower score. Testing will be done in a seated position.

#### AIS Sensory Assessment of the target hand at 8 weeks, 6 months and 12 months

The AIS sensory assessment is part of the assessment for the International Standard for Neurological Classification of Spinal Cord Injury. It involves testing pin-prick and light touch sensation at key points representing each cervical dermatome. Pin-prick and light-touch sensation of each dermatome is separately scored on a 3-point scale. Scores will be summed to give a total possible score of 32 where a higher score indicates better sensation than a lower score.

#### AsTex^® ^Sensory Test of the target hand at 8 weeks, 6 months and 12 months

The AsTex^® ^sensory test assesses the texture discrimination capabilities of the thumb and fingertips. It requires participants to run their thumbs, index fingers and little fingers along a grooved acrylic surface with logarithmically decreasing spaces and to stop when they perceive it as smooth [20]. The mean texture discrimination index (TDI) of the finger, thumb and little finger will be derived from three trials for each digit. The results will be interpreted with respect to age-related normative values where a lower score reflects better texture discrimination than a higher score.

#### AuSpinal Assessment of the target hand at 8 weeks, 6 months and 12 months

The AuSpinal Hand Assessment is a unilateral measure of hand function [21]. It consists of a number of hand-related tasks using the following objects: a key, nut/bolt, coin, credit card, sweet, telephone receiver and soft drink can. Scores will be summed to give a total possible score of 86 where a higher score reflects better hand function than a lower score.

#### The Goal Attainment Scale (GAS) of the target hand at 8 weeks

The GAS captures improvements on self-selected goals [22-24]. Prior to baseline assessments, participants will identify two personal goals related to use of their target hands in conjunction with their treating therapists. The goals will be set according to the SMART principle, that is, the goals will be specific, measurable, attainable, realistic and timely [25]. Participants will rate their perceptions of attainment at the 8-week assessment with the assistance of blinded assessors. The two goals will be rated on a 5-point scale, where "0" denotes the expected level of achievement; "+1" and "+2" are respectively "a little" and "a lot" better than expected, whilst "-1" and "-2" are correspondingly "a little" and "a lot" less than expected. The scores for the two goals will be averaged with a higher score reflecting better achievement of goals than a lower score.

#### The Capabilities of Upper Extremity (CUE) of the target hand at 8 weeks, 6 months and 12 months

The CUE is an interview-based questionnaire about perceptions of upper limb function specifically designed for participants with tetraplegia. Fifteen questions of the CUE related to unilateral hand and upper limb function will be used. The questions address reaching and lifting, pulling and pushing, wrist actions as well as hand and finger actions. Participants will rate their abilities to perform the 15 items on a seven-point scale from 1 to 7 [26]. Scores will be summed to give a total possible score of 105 where a higher score reflects better upper limb function than a lower score.

#### Assessment of Quality of Life - 8 (AQoL - 8) at 8 weeks, 6 months and 12 months

The AQoL-8 is a health-related quality of life instrument [27,28]. It is a self-administered 8-item questionnaire that provides utility scores varying between -0.04 (worse than death), 0 (death) and 1 (perfect health) where a higher score reflects better quality of life than a lower score.

#### Health Utilities Index Mark 3 (HUI3) at 8 weeks, 6 months and 12 months

The HUI3 is a self-administered questionnaire of health-related quality of life [29]. It covers eight attributes (vision, hearing, speech, ambulation, dexterity, emotion, cognition and pain) with five or six levels for each attribute. It is widely used in population health surveys, clinical studies and cost-utility analyses. HUI3 discriminates various aspects of burden associated with chronic conditions and describes the differences in overall health-related quality of life levels. Like the AQoL, it provides utility scores varying between -0.36 and 1 where a higher score reflects better quality of life than a lower score.

#### The self-care subscale of the Spinal Cord Independence Measure - Version III (SCIM) at 8 weeks, 6 months and 12 months

The SCIM was designed specifically for patients with SCI. The SCIM focuses on the ability to perform basic everyday tasks and takes into consideration the economic burden of disability as well as the impact of disability on overall medical condition and comfort [30]. The self-care subscale consists of six items which address ability to feed (score 0 to 3), bathe upper body (scored 1 to 3), bathe lower body (scored 1 to 3), dress upper body (scored 1 to 4), dress lower body (scored 1 to 4) and groom (scored 0 to 3). Scores will be summed to give a total possible score of 20 where a higher score reflects more independence than a lower score.

#### Participant Perception of Treatment Effectiveness at 8 weeks

Participants will be required to rate their perceptions about changes in hand function on a 15-point scale where zero indicates no change, +7 indicates "a very great deal better" and -7 indicates "a very great deal worse" [31].

#### Economic outcomes

Economic evaluation will determine whether the experimental intervention is more cost-effective than the control intervention. Cost-effectiveness analysis will measure incremental costs in the two groups in relation to the ARAT, health utility and quality of life measures. The primary focus will be the health care sector. All relevant costs associated with delivery of experimental and control interventions will be used. The cost of treatment will be estimated using standard costs for therapy and actual costs of training equipment expressed as a mean cost of treatment per participant. Community-based resource use in the 12-month follow-up period will include data on visits to GPs, specialists or other health care providers, pharmaceutical costs, as well as data on resource use specifically relating to levels of independent functioning (e.g. aids, equipment, community services, home help, home maintenance, meals on wheels, transport, formal and informal care).

#### Burden of the experimental interventions on participants

At the 8-week assessment, all participants will be asked by the blinded assessors to rate on a 10- point category rating scale their perceptions about the convenience or inconvenience of the hand training received to the target hand. This will be used to gauge the burden of the experimental intervention on participants. It will not be used as an outcome measure.

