### Outcome assessments

Measurements will occur at baseline, 8 weeks after the commencement of the intervention period (8 weeks), and then at 6 months and 12 months after randomisation (see Table 1). There is a 3-week period after randomisation when all participants receive usual care prior to the commencement of the 8-week intervention period. This is to allow time for the delivery of the FES garments for experimental participants (these are custom made in Canada). For this reason, the 8-week assessments are 8 weeks after commencement of the intervention period but 11 weeks after randomisation.

**Table 1 T1:** Timeline of participants' progression through the trial

week -3	week -1	week 0	weeks 0 - 3	weeks 4 - 12	week 13 ^†^	weeks 14 - 25	week 26^§^	weeks 27 - 51	week 52^§^
screening	baseline assessment by blinded assessor	concealed random allocation	usual care for all participants^€^	8-week intervention **Exp**: Instrumented exercise workstation, FES and usual care **Control**: usual care	8-week assessment by blinded assessor	usual care for all participants	6-month assessment by blinded assessor	usual care for all participants	12-month assessment by blinded assessor

^† ^plus or minus 1-week window for commencement; 1-week window for completion upon commencement

^§ ^plus or minus 1-week window for commencement; 1-week window for completion upon commencement

^€ ^this 3-week period is to allow time for the ordering and delivery of the personalised FES garment for experimental participants

All assessments will be made by research therapists blinded to group allocation. Any inadvertent unblinding of assessors will be reported. In addition, the success of blinding will be estimated by asking assessors to guess participants' group allocations at the completion of each post-randomisation assessment.

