## Discussion

This trial will provide information about the effectiveness of an intensive task-specific hand training program provided with FES through an instrumented exercise workstation. Hand function in people with tetraplegia is central to their quality of life. Any treatment that can improve their hand function has the potential to make real and important differences to the lives of those affected by SCI.

This trial will adhere to key methodological principles important for minimising bias and will be reported according to the CONSORT guidelines. For example, allocation will be concealed and randomised, assessors will be blinded and analyses will be performed on an intention-to-treat basis. Therapists and participants will not be blinded due to the nature of the intervention.

One primary outcome and a number of secondary outcomes will be used. The primary outcome reflects unilateral hand function. The secondary outcomes include measures of impairment, activity limitation and participation restriction, and encompass both objective measures as well as participants' perceptions.

It is anticipated that this trial will take three years to complete. Recruitment commenced in December 2009 with the first participant randomised in February 2010. Recruitment will continue until mid 2011. The one-year follow up assessments will be completed in 2012.

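### Having the blinded assessors ask participants to rate the burden of their hand training opens an avoidable route to disclosure of allocation

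*Protocol article*

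**What the plan says.** The section on the burden of the experimental interventions sets a question for the 8-week visit: "all participants will be asked by the blinded assessors to rate on a" 10-point category scale "their perceptions about the convenience or inconvenience of the hand training received to the target hand". Its purpose is to gauge how burdensome the experimental programme is, and the section adds: "It will not be used as an outcome measure".

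Four other statements bear on this:

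- Discussion: "Therapists and participants will not be blinded due to the nature of the intervention".
- Outcome assessments: "All assessments will be made by research therapists blinded to group allocation".
- Primary outcome: "Modified Action Research Arm Test (ARAT) for the target hand at 8 weeks". On how it is rated: "All tasks will be scored on a 4-point scale from 0 to 3", with a maximum total of 57.
- Outcome assessments, on protecting the blind: "Any inadvertent unblinding of assessors will be reported". Assessors also guess each participant's group at the end of every assessment after randomisation.

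**The concern.** Participants and treating therapists know the allocation, so assessor blinding is the main protection against detection bias. The ARAT, the manual muscle test and the AuSpinal assessment all depend on an assessor's grading of what the participant does.

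Most questions at the visit concern ability, goals or change in hand function. The burden question concerns the training itself, which is what separates the groups. Experimental participants have had an extra hour of workstation and FES training five times a week, on top of usual care. Someone asked how inconvenient that was may well mention the workstation, the garment or the daily session.

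This is an instruction that the article states, not a detail that it leaves out. It gives the question to the staff whose ignorance of allocation the trial relies on, and it does so for an item that no outcome analysis needs.

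**Working it through.** **1. The article's statements side by side**

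| Element | What the article fixes |
|---|---|
| Who asks | The blinded assessors |
| Who answers | All participants, who know their group |
| Subject | The hand training received to the target hand |
| Form of answer | A rating on a 10-point scale; the type of training is not asked |
| Visit | 8 weeks, the time point of the primary outcome |
| Use of the rating | Gauge of burden, not an outcome |
| Order relative to the ARAT | Not stated |
| Same assessor at 6 and 12 months | Not stated |
| Safeguards named | Reporting of unblinding; allocation guess |

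**2. When each score could be affected**

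- 8-week ARAT, strength and AuSpinal scores: only where the burden item is asked before the test concerned.
- 6- and 12-month scores: only if the assessor who heard the answer returns.
- Allocation guess at 8 weeks: it is made when the assessment is complete. If the burden item is part of that assessment, it comes before the guess and may influence it. The guess would then partly reflect what was learned from the burden item, possibly after the tests had been scored.

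**3. The plan's own sample size, reproduced to set the scale**

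Inputs from the Sample Size section: difference 5.7, SD 14, correlation 0.8, two-sided 5%, power 80%, drop-out 10%.

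- Adjusted SD = 14 × √(1 − 0.8²) = 14 × 0.6 = 8.4.
- n per group = 2 × (1.960 + 0.842)² × 8.4² / 5.7² = 34.1, rounded up to 35.
- With drop-out: 35 / 0.9 = 38.9, rounded up to 39 per group, or 78 in total. This agrees with the article.
- Standard error of the adjusted difference with 35 per group = 8.4 × √(2/35) = 2.01 points.

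**4. Illustration of a possible bias**

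The article gives neither a disclosure rate nor a size of scoring bias, so both are assumed. The maximum of 57 at 3 points per task implies 57 / 3 = 19 tasks. Assume that an assessor who learns that a participant is in the experimental group grades 2 of the 19 tasks one step higher, which adds 2 points, and that control scores do not change.

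Mean shift = share disclosing before ARAT scoring × 2 points. The false-positive rate with no true effect = 1 − Φ(1.96 − shift/2.01) + Φ(−1.96 − shift/2.01).

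| Share of experimental participants disclosing | Mean shift (points) | Share of 5.7 | False-positive rate (nominal 5%) |
|---|---|---|---|
| 0%, or item asked after the ARAT | 0 | 0% | 5.0% |
| 10% | 0.2 | 4% | 5.1% |
| 25% | 0.5 | 9% | 5.7% |
| 50% | 1.0 | 18% | 7.9% |
| 100% | 2.0 | 35% | 17% |

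**The case against.** The strongest defence is that the item is neutral between arms. It goes to everyone, asks for a number, and concerns hand training that both groups receive: usual care includes at least three 15-minute one-to-one sessions a week directed at the target hand. Disclosure needs an unprompted remark. This stands. A reader might infer that any natural answer reveals the group, but the article describes a rating and not an account of the training.

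A second point is that test order and advice to participants not to discuss their treatment belong in a full protocol or assessor manual, which is not shown. That also stands: their absence from an article is no finding. A reader might therefore go too far in concluding that blinding fails at the primary time point, or that assessors carry the knowledge into later visits. The first depends on item order and the second on assessor continuity, and the article settles neither. Nor can the 35% figure be taken as the expected bias, since it requires every experimental participant to disclose before ARAT scoring.

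Third, the article does monitor blinding. The reporting of unblinding and the allocation guess would give some indication of how much occurred. But they detect disclosure and do not prevent it, and the guess may itself be affected by the item.

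Finally, a neutral assessor is a defensible person to ask about burden, because a participant may be reluctant to complain to the therapist who delivered the training. This is a fair reason not to pass the question to the treating therapist. It is no reason to give it to the blinded assessor when a sealed form is available.

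**Conclusion.** The concern holds as an avoidable risk to assessor blinding, not as a demonstrated failure of it. The article itself assigns the question to the blinded assessors, puts it to participants who know their group, and places it at the visit where the assessor-scored primary outcome is taken.

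The size cannot be determined from the article. Under the assumed 2-point upgrade, the shift in the 8-week ARAT difference runs from zero, where the item follows the ARAT or nobody discloses, to 2.0 points with universal earlier disclosure. Disclosure by a quarter of experimental participants would give 0.5 points and a false-positive rate of about 5.7%. The planned sample size is reproduced and is not in question. The change is worth making because the risk brings no benefit to any outcome and costs little to remove.

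**What to change.** Amend the section on burden so that the blinded assessor does not ask for the rating. Instead, participants record it on a self-completed form, sealed on completion, after the assessor has submitted that visit's scores and the allocation guess. Where limited hand function makes help necessary, it should come from existing staff who neither assess outcomes nor delivered the training, which also avoids courtesy bias. The trial already uses self-administered questionnaires (AQoL-8 and HUI3), so the format is not new to it.

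The cost is slight extra logistics for one item that is not an outcome. No endpoint, sample size or analysis changes. If the full protocol already places the item after all assessor-scored tests, the 8-week scores are protected, but the change still protects the allocation guess and any later visit by the same assessor.

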### Statistical analyses

#### Sample Size

A sample size of 78 (i.e. 39 per group) will be used based on 80% power, a between-group minimally worthwhile treatment effect on ARAT scores at 8 weeks of 5.7 points, a two-sided hypothesis test, an alpha level of 5%, a standard deviation of 14 points [personal communication; [name], 2009], an ANCOVA model that includes baseline ARAT score as a covariate, a correlation between baseline and 8 weeks ARAT scores of at least 0.8, and an adjustment to allow for a drop-out rate of 10%. All data are based on the results of a similar pilot study conducted in Canada [personal communication; [name], 2009]. Stata software (Version IC 10, StataCorp, College Station, TX) was used for sample size calculations.

#### Analysis

The primary analysis of ARAT score at 8 weeks will be performed using an ANCOVA model that includes treatment group and site as factors, and the baseline ARAT score as a covariate. All secondary outcomes (including the ARAT at 6 months and 12 months) will be analysed using a mixed model repeated-measures (MMRM) approach where applicable (i.e. where data are collected at 8 weeks, 6 months and 12 months). Multiple imputation analysis will be performed to account for the effect of missing data.

Analyses will be performed by a blinded and independent statistician according to the intention-to-treat principle and using the full dataset comprising all randomised participants. In addition, the primary analysis on the 8 weeks ARAT data will be repeated using a per protocol dataset. This dataset will only comprise participants who adhered to all aspects of the protocol and received at least 80% of training sessions (i.e., control participants who received at least 80% of the 15-minute sessions of one-to-one hand therapy and experimental participants who received this as well as 80% of the training sessions with the instrumented exercise workstation and FES). All analyses will be performed using Stata (Version 11 or higher).

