### Intervention

#### Control participants

Control participants will receive usual care and will not receive any electrical stimulation to the target hand or upper limb nor will they be exposed to the instrumented exercise workstation.

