#### Experimental participants

In addition to the usual care provided to all participants, experimental participants will receive one hour of one-to-one hand training directed at the target hand with a research therapist, five times per week for 8 weeks. The training will consist of an intensive task-specific hand training program provided through an instrumented exercise workstation (ReJoyce) in conjunction with FES. The hand activities will involve playing computer games while practising functional tasks (including reaching, grasping, manipulating, pulling, rotating and releasing) using different manipulanda (see Figure 1).

The exercises and computer games will be progressed so that, as hand function improves, more difficult hand exercises and games will be introduced. Each training session will be one hour long and participants will be required to use the instrumented exercise workstation and FES as much as possible during this time.

The FES will be provided through 5 cm diameter electrodes embedded in wetted cloth pads backed with stainless steel mesh. The electrodes will be incorporated into a customised garment. The cathode of each electrode pair will be placed over the proximal end of each target muscle. The reference electrode will be placed on the dorsal surface of the forearm and just proximal to the wrist joint. The FES will be provided in trains of stimuli (50 per second: 200 μs biphasic, current-controlled pulses). The FES will be administered to any or all of the muscles that facilitate opening or closing of the hand including the flexors and extensors of the wrist, fingers and thumb.

FES will be triggered by participants clicking their teeth. The tooth clicks (vibrations) will be detected by a wireless earpiece, similar to a hearing aid, which sends a radio signal to the stimulator garment. This in turn stimulates the hand to open or close, allowing participants to grasp or release objects. The stimulator system has been tested and approved by the Canadian Standards Association. As it is not yet approved in Australia, the stimulator is being used for this trial under the Clinical Trials Notification Scheme of the Therapeutic Goods Administration of Australia.

If participants miss any treatments during the 8-week intervention period, the missed sessions will be offered to participants on weekends or during an optional additional week at the end of the 8-week intervention period.

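### The per-protocol repeat of the primary analysis screens the two arms on different post-randomisation attendance rules, so it is open to selection bias of unknown direction; label it descriptive and add an instrumental-variable estimate

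*Protocol article*

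**What the plan says.** The Analysis section of the protocol article sets the main approach "according to the intention-to-treat principle and using the full dataset comprising all randomised participants". The primary model is an ANCOVA of 8-week ARAT with treatment group and site as factors and baseline ARAT as covariate. The section then adds: "In addition, the primary analysis on the 8 weeks ARAT data will be repeated using a per protocol dataset". Membership of that set is defined as follows: "This dataset will only comprise participants who adhered to all aspects of the protocol and received at least 80% of training sessions". The rule is spelled out by arm:

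- Control arm: "control participants who received at least 80% of the 15-minute sessions of one-to-one hand therapy".
- Experimental arm: "experimental participants who received this as well as 80% of the training sessions with the instrumented exercise workstation and FES".

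Workstation training is scheduled "five times per week for 8 weeks" (Experimental participants section). If sessions are missed, "the missed sessions will be offered to participants on weekends or during an optional additional week at the end of the 8-week intervention period". Controls receive no electrical stimulation to the target hand or upper limb, "nor will they be exposed to the instrumented exercise workstation". The Quality assurance section says that treatments in both arms are recorded. The Discussion says that participants and therapists are not blinded.

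**The concern.** Randomisation makes the arms comparable as randomised. The per-protocol set keeps people according to what they did afterwards, and the filter differs by arm. An experimental participant who would not sustain the training programme is removed. A control who would not have sustained it stays in, because no one can observe how that control would have attended. Tolerance, general health, motivation and perceived progress could all affect both attendance and the 8-week ARAT, and neither site nor baseline ARAT captures them. The trial is open-label for participants and therapists, so attendance can also respond to how recovery seems to be going.

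What is at stake is interpretation. The article attaches no caveat to the repeat. A larger effect in the per-protocol set could be taken as evidence that the training works when it is attended, when part of the difference may reflect who was retained.

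**Working it through.** **Planning figure reproduced.** Inputs from the Sample Size section: difference 5.7, SD 14, baseline to 8-week correlation 0.8, two-sided alpha 5%, power 80%, dropout 10%.

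- Residual SD = 14 × √(1 − 0.8²) = 14 × 0.6 = 8.4.
- n per arm = 2 × (1.96 + 0.84)² × 8.4² / 5.7² = 34.1, so 35.
- 35 / 0.9 = 38.9, so 39 per arm and 78 in total, as stated.

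**The screens in sessions.**

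- Workstation: 5 × 8 = 40 sessions, and 80% is 32.
- Usual care: at the stated minimum of three sessions a week, 3 × 8 = 24; 80% is 19.2, so 20.
- Controls therefore need 20 of 24. Experimental participants need 20 of 24 and 32 of 40.

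**Bias with no treatment effect.** The documents give no attendance rates and no link between attendance and recovery, so these are assumptions. Each person has a residual outcome (SD 8.4, what remains after baseline ARAT) and two normal attendance propensities, one for usual care and one for the workstation. The propensities correlate 0.5 with each other and rho with the residual outcome. Bias = mean residual of those passing both rules − mean residual of those passing the usual-care rule only, from 1,000,000 draws per setting. Columns give the share meeting the usual-care rule / the share meeting the workstation rule.

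| rho | 90% / 90% | 90% / 80% | 90% / 70% | 80% / 60% |
|---|---|---|---|---|
| −0.3 | −0.33 | −0.65 | −0.96 | −1.11 |
| 0 | 0 | 0 | 0 | 0 |
| 0.2 | +0.22 | +0.43 | +0.65 | +0.75 |
| 0.3 | +0.33 | +0.64 | +0.97 | +1.11 |
| 0.5 | +0.54 | +1.08 | +1.61 | +1.85 |

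The largest entry is 1.85 / 5.7 = 32% of the target, with a type I error of about 0.11 in the per-protocol test. With 35 assessed per arm, the 90% / 70% setting retains about 32 controls (90%) and 23 experimental participants (67%).

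The upper end depends on how the two propensities are related. With 60% meeting the workstation rule and rho 0.5:

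- one shared propensity (90% meeting the usual-care rule) gives 0.5 × 8.4 × (0.644 − 0.195) = 1.9;
- two independent propensities give 0.5 × 8.4 × 0.644 = 2.7.

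Here 0.644 and 0.195 are the standardised mean shifts from keeping the top 60% and the top 90%.

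**What an instrumental-variable estimate would give.** Controls have zero workstation sessions by design. With one binary instrument, two-stage least squares is therefore the adjusted ITT difference divided by the adjusted difference in mean sessions attended. For illustration, an ITT effect of 5.7 with an assumed mean of 32 sessions gives 5.7 / 32 = 0.178 points per session, or 0.178 × 40 = 7.1 for 40 sessions if dose-response is linear.

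If exposure is instead a yes/no indicator of reaching 80%, the estimate is ITT / p, where p is the share reaching it. An ITT of 5.7 gives 6.3, 7.1, 8.1 or 9.5 at p = 90%, 80%, 70% or 60%. This requires that attendance below the threshold does nothing. If partial attenders gain half of a full effect of 5.7, the error is 5.7 × 0.5 × (1 − p) / p, which is 0.3, 0.7, 1.2 or 1.9 points too high at the same values of p.

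**The case against.** The best defence is that the repeat is supplementary. The primary conclusion rests on all randomised participants, and no alpha, power or decision depends on the per-protocol set. In an add-on design, different rules by arm are what receiving the assigned treatment means, because controls have no workstation sessions to attend. All of this stands, and it limits the weight of the point.

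Attendance may also be high. Participants are inpatients expected to stay 12 weeks, people with conditions likely to affect adherence are excluded, and missed training is offered again. Controls who fail the usual-care rule are removed too, which offsets part of the selection if attendance habits are shared. This supports the lower end of the range but does not restore the randomised comparison.

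It can also be said that labelling, or adding a complier analysis, belongs to a statistical analysis plan that is not shown. The absence of such an analysis is indeed no fault of the article. The point concerns an analysis that the article does state, with its selection rule fixed.

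Three stronger readings are tempting, and the documents do not support them:

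- A reader might infer that the per-protocol estimate is certainly biased upward. Sign and size depend on a link between attendance and recovery that the documents do not give.
- A reader might take this repeat to be the only supporting analysis of the primary endpoint. The same section also states multiple imputation for missing data.
- A reader might expect an instrumental-variable estimate to be unbiased. It keeps the randomised comparison, but it is consistent only under its stated assumptions.

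**Conclusion.** The point holds as a risk in a stated supplementary analysis. Selection is on post-randomisation attendance, with two screens in one arm and one in the other, and adjustment is for site and baseline ARAT only. With 60% to 90% of participants assumed to meet the workstation rule, rho from 0.2 to 0.5 and a 0.5 correlation between the two attendance propensities, the spurious effect is about +0.2 to +1.9 points, or 4% to 32% of 5.7. It is zero at rho 0 and about −0.3 to −1.1 at rho −0.3. Equal rules in both arms would not guarantee balance either, since the extra training could change attendance at usual care. The intention-to-treat primary analysis and the sample size of 78 stand. This is a cheap improvement and not a threat to the trial's main result.

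**What to change.** Keep the per-protocol repeat, but label it descriptive and say that its arms are selected by different attendance rules.

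Add one adherence analysis: two-stage least squares on 8-week ARAT, with randomised group as instrument, recorded workstation sessions attended as exposure (zero for controls), and site and baseline ARAT as covariates, in all randomised participants and with the same handling of missing data as the primary analysis. Report the effect per session, or scaled to 40 sessions under a stated linear dose-response. State the exclusion restriction: assignment affects 8-week ARAT only through workstation sessions. In an open-label trial this would fail if, for example, usual care or effort differed by arm for other reasons. If a yes/no 80% threshold is used instead, state the further assumption that attendance below it has no effect.

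The cost is some wording and one model in Stata, which is already the planned software, on data already being recorded. The interval will be wider and the assumptions cannot be tested. The estimate addresses workstation attendance, not adherence to every part of the protocol, so it answers a narrower question than the per-protocol set was meant to.
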